### Randomisation

A computer generated 1:1 allocation sequence (in random permuted blocks of either four or six) will be created by an independent operator who is not directly involved with the study. Allocation concealment will be achieved using sequentially numbered, sealed opaque envelopes. An intravenous cannula will be inserted and standard monitoring applied, and then based on the randomization, the anaesthetist will perform either an ultrasound guided BPB as necessary or ask the operating surgeon to undertake local anaesthetic infiltration.

Patients in the Ultrasound Guided BPB group will receive an ultrasound guided brachial plexus block. A supraclavicular block will be performed unless there is a contraindication, in which case an axillary block will be used. A 1:1 mixture of 0.5% L-bupivicaine and 1.5% lignocaine with adrenaline (1 in 200,000) will be injected, using a minimum of 25 mls and up to a volume of 40 ml [20]. Maximum dose limits of 2 mg/kg for bupivicaine and 7 mg/kg for lignocaine with adrenaline will be observed, recognising that these are additive. The time taken to perform the block and any technical problems during block insertion will be recorded in the patient’s case report file (intravascular puncture, paraesthesia). Measurements of the sensory block of the musculocutaneous, median, radial and ulnar nerves will be recorded every five minutes by a non-blinded observer using a previously validated 3-point scale using a cold test: 0 = no block, 1 = analgesia (can feel touch but not cold) and 2 = anaesthesia (patient cannot feel touch) [21]. Motor block of the musculocutaneous, median, radial and ulnar nerves will be graded using a previously validated scale as either 0 = no block, 1 = paresis, 2 = paralysis [21]. Measurements will be continued until either the sensory block is adequate in the operative area distribution or a maximum of 20 minutes has elapsed at which point the block will be supplemented by targeted axillary or midhumeral supplementation as appropriate using ultrasound. If a BPB block fails despite supplementation, LA infiltration will be used. This will be recorded as a failed block. If intravenous opioid analgesia is required for operative site discomfort, the BPB will be recorded as a failed block. Anaesthetists performing ultrasound guided BPBs in this study will have been deemed competent to perform this technique by the principle investigator.

Patients in the Local Anaesthetic Infiltration group will receive infiltration of local anaesthetic into the surgical site by the operating surgeon under sterile conditions using a combination of 0.5% L-bupivicaine prior to incision and 1% lignocaine topically after the wound is opened. Maximum dose limits of 2 mg/kg for bupivicaine, and 3 mg/kg for lignocaine will be observed, recognising that these are additive.

Using the technique described above, at the points marked on the skin the internal diameters of the cephalic and basilic veins will again be measured. Because after a successful BPB patients will generally have an immobile, vasodilated, warm arm, blinding from this stage will be difficult. The average of three measurements at each position will again be calculated. Similarly, the arterial blood flow will be measured by Doppler ultrasound as described previously, and again the average of three measurements will be recorded. The veins and artery at the proposed surgical site will also be examined and mapped using ultrasound by the surgeon. The operating surgeon will use this information to decide on the final site for the fistula. Any deviation from the pre-operative plan based on anatomical information obtained using ultrasound at this stage will be recorded.

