### Patients and enrolment

Patients scheduled to undergo primary AVF creation will be invited to participate in the study during their pre-assessment clinic visit staffed by the surgeon and the pre-assessment anaesthetic nurse. Inclusion criteria are English-speaking adults aged 18 to 85 who are competent to give consent scheduled for primary AVF formation at either the radial or brachial artery. Exclusion criteria are allergy to local anaesthetic, coagulopathy, infection at the anaesthetic or surgical site, patient preference for general or alternative anaesthesia, significant peripheral neuropathy or neurologic disorder affecting the upper extremity, pregnancy, previous AVF creation on the ipsilateral arm, known cephalic vein occlusion, central vein stenosis, brachial or radial artery stenosis and vein or artery less than 1.8 mm, as measured by ultrasound.

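### If the additive dose limits mean that the two fractions sum to at most 1, the 25 ml minimum block volume cannot be given within them to patients under about 58 kg

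*Protocol article*

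**What the plan says.** The instructions for the block group are in the protocol article, Methods, Randomisation. The solution is fixed first: "A 1:1 mixture of 0.5% L-bupivicaine and 1.5% lignocaine with adrenaline (1 in 200,000) will be injected". The same sentence then sets the volume: "using a minimum of 25 mls and up to a volume of 40 ml". The sentence after it sets the cap: "Maximum dose limits of 2 mg/kg for bupivicaine and 7 mg/kg for lignocaine with adrenaline will be observed, recognising that these are additive".

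Two later steps can add local anaesthetic. If sensory block is inadequate after at most 20 minutes, "the block will be supplemented by targeted axillary or midhumeral supplementation as appropriate using ultrasound". After that, "If a BPB block fails despite supplementation, LA infiltration will be used". No volume is given for either step.

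Under Patients and enrolment, eligibility begins "Inclusion criteria are English-speaking adults aged 18 to 85 who are competent to give consent". Neither the inclusion nor the exclusion criteria mention body weight, and the Randomisation section gives no weight-based exception to the 25 ml minimum.

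**The concern.** The minimum volume and the dose limits are both worded as mandatory and stand next to each other. One is fixed in millilitres whatever the patient's size, and the other scales with body weight. There must therefore be a weight below which they cannot both be met. The question is whether that weight falls within the range of adults the trial may enrol.

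If it does, the anaesthetist treating a lighter patient in the block group must either exceed a stated safety limit or give less than the specified intervention, and the text does not say which instruction prevails. The article itself, under Adverse event reporting and safety, names systemic local anaesthetic toxicity as a serious though rare complication of regional anaesthesia. The effect is confined to one arm.

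**Working it through.** The article states no milligram dose or threshold weight, so there is no figure of its own to reproduce. The check uses only its concentrations, volumes and limits.

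**Inputs (Randomisation section)**
- Stock solutions: 0.5% = 5 mg/ml bupivacaine; 1.5% = 15 mg/ml lignocaine.
- 1:1 by volume: each ml of mixture holds 2.5 mg bupivacaine and 7.5 mg lignocaine.
- Volume V: at least 25 ml, at most 40 ml.
- Limits: 2 mg/kg and 7 mg/kg, additive.

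**Rule assumed for additive limits.** With body weight W in kg, the fractions of the two limits sum to at most 1:

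2.5V/(2W) + 7.5V/(7W) ≤ 1, so W ≥ 1.25V + 1.0714V = 2.3214V.

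**Minimum volume, 25 ml**
- Content: 25 × 2.5 = 62.5 mg and 25 × 7.5 = 187.5 mg.
- Lowest compatible weight: 62.5/2 + 187.5/7 = 31.25 + 26.79 = 58.04 kg.
- Share of the combined limit, 58.04/W: 129% at 45 kg, 116% at 50 kg, 106% at 55 kg, 97% at 60 kg, 83% at 70 kg.

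**Ceiling, 40 ml**
- Content: 100 mg and 300 mg.
- Lowest weight at which the full ceiling fits: 100/2 + 300/7 = 50 + 42.86 = 92.86 kg.

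**Room left after 25 ml, in the same mixture.** The largest volume within the limits is W/2.3214. That is 25.85 ml at 60 kg and 30.15 ml at 70 kg, leaving about 0.85 ml and 5.15 ml. These figures describe the protocol's own limits and are not recommendations.

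**How far the 25 ml threshold depends on the reading**

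| Reading | Lowest compatible weight at 25 ml |
|---|---|
| Each limit applied alone | the larger of 62.5/2 = 31.3 and 187.5/7 = 26.8, so 31.3 kg |
| Fractions sum to at most 1 | 58.0 kg |
| Each limit halved because two agents are used | the larger of 62.5/1 = 62.5 and 187.5/3.5 = 53.6, so 62.5 kg |
| Percentages are concentrations in the final mixture, fractions sum to at most 1 | 25 × 5/2 + 25 × 15/7 = 116.1 kg |

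Only the first reading brings the threshold down to a weight few adults would fall below, and it leaves the word additive with no effect.

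**The case against.** The strongest reply is that the cap is explicit, directly follows the volume range and admits no exception. Anaesthetists judged competent would follow it and simply give less than 25 ml. That is probably what would happen, and it limits the practical risk. It does not remove the conflict, because giving less departs from a stated minimum and the text does not subordinate the minimum to the cap.

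It can also be said that the sum-of-fractions rule is not written down. That is correct, and the 58 kg figure is conditional on it. With each limit taken alone the conflict shrinks to patients under 31.3 kg.

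Four stronger readings may tempt a reader, and the article supports none of them.

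- *That the 40 ml figure breaches the limits in everyone under about 93 kg.* It is an upper bound beneath a binding cap. From about 58 kg upwards a compliant volume of at least 25 ml exists, so nothing compels a breach. What remains true is that the top of the range cannot be reached within the additive limits below about 93 kg.
- *That the two lignocaine limits contradict each other.* For the infiltration group the article sets 2 mg/kg for bupivacaine "and 3 mg/kg for lignocaine will be observed, recognising that these are additive". That applies to 1% lignocaine with no adrenaline mentioned, in the other arm. The 7 mg/kg figure is for lignocaine with adrenaline. They are limits for different preparations.
- *That supplementation and rescue infiltration break the limits.* Neither step has a stated volume and neither is exempted from the limits. A journal article may leave such volumes to the full protocol. The arithmetic shows only that little room remains just above 58 kg.
- *That the trial's result is at risk.* Under Sample size and statistical considerations, the intention-to-treat analysis keeps patients whose block failed or who could not receive the allocated treatment. No effect on the primary comparison is shown.

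**Conclusion.** The Randomisation section contradicts itself for lighter patients. The mandatory 25 ml minimum and the additive dose limits cannot both be met below about 58 kg, and 25 ml uses 116% of the combined limit at 50 kg. No eligibility criterion keeps such patients out.

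This rests on three assumptions: 1:1 means equal volumes of the two stock solutions, the bupivacaine limit applies to the L-bupivacaine in the mixture, and additive means that the fractions of the limits sum to at most 1. The number of patients under 58 kg who would be enrolled cannot be known from the article.

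The point matters for patient safety and for whether the block is delivered as specified. It does not touch the primary analysis, and on that ground it ranks below a must-fix.

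**What to change.** The investigators should reconcile the minimum volume with the additive limits in the Randomisation section, so that one consistent instruction applies at every eligible body weight. They should write out what additive means. The reconciled text should also account for the cumulative total, including block supplementation and any rescue infiltration after a failed block. Which instruction gives way is a clinical decision for them, and no dose, volume or rule is proposed here.

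The cost is a short clinical amendment. Design, sample size and analysis stay as they are.

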### Blinding

The allocation sequence will be accessed only when study data collection is complete or in any instance where unblinding of the study is thought to be essential in the provision of appropriate patient care. Due to the nature of the BPB and LA techniques, blinding of the patient, operating surgeon and observer measuring immediate post-anaesthetic flows is not possible. All further post-operative measurements, including the primary outcome, will be undertaken by a blinded observer.

### Intra-operative management

The anaesthetist looking after the patient in theatre will play no part in data analysis and will record the intra-operative proceedings as normal. The medications used to perform the two potential procedures will not be recorded on the anaesthetic chart. The patient’s participation in this study and the two possible anaesthetics that may have been received will be documented on the anaesthetic chart using a pre-made sticky label. Documentation of the anaesthetic procedures, including adverse events, will be kept in the patient’s case report file. The randomisation code may be accessed if deemed necessary in the provision of optimal patient care.

The patient will receive sedation if required and as directed by the anaesthetist. All medications, with the exception of the medications used to perform the BPB or local anaesthetic infiltration, will be detailed in the anaesthetic record.

All AVF procedures will be carried out at either the wrist, forearm or antecubital fossa. A radio-cephalic AVF will be fashioned through a longitudinal or equivalent incision and brachiocephalic AVFs fashioned using a horizontal or equivalent incision. Heparinized saline may be used to distend the vein. After sufficient mobilisation of the vein, an end-to-side or side-to-side anastamosis will be created using 6.0 or 7.0 non-absorbable suture. AVF patency peri-operatively will be confirmed by palpating for a thrill and listening for a bruit. If at this stage there is no evidence of patency, this will be recorded and surgical revision urgently undertaken if appropriate.

### Postoperative management

After surgery, patients will be taken to the recovery room and monitored according to standard hospital policy. Patient satisfaction and pain during the procedure will be assessed at this point. Patients will be discharged if they meet day surgery criteria as per hospital policy.

At a time period of one month, three months and one year, a blinded observer will examine AVF clinical patency by palpating for a thrill and auscultating for a bruit. At all these time points patients will be attending routine follow-up clinics or have commenced haemodialysis. Lack of both a thrill and a bruit will result in the fistula being defined as not patent. At the same time, brachial artery volume flow will be measured (as a surrogate for AVF flow) by a blinded observer using Doppler ultrasound as described previously. An average of three measurements will again be made in order to reduce both intra and inter-observer variation. Measurement of brachial artery flow is more reproducible than AVF flows and less prone to intraobserver variability [22]. The probe will be positioned at a distance of 2 to 5 cm cranial to the arterio-venous anastamosis. The point of measurement will be recorded and measurements at three months and one year made at the same position. A minimum of six weeks after AVF creation will be allowed to elapse before the first venipuncture for HD. The flow during the first cannulation of the fistula will be recorded by a blinded observer in the renal patient registry, and also at three months and one year if HD has been commenced at these time points. Finally, at each time point of one and three months and one year it will be noted by a blinded observer if there has been any infection of the AVF requiring antibiotics.

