### Objectives and outcome measures

This study aims to compare local anaesthetic infiltration to a BPB anaesthetic technique for the surgical creation of an AVF, assessing in particular whether an increase in flow at the time of surgery with a BPB alters long-term outcome. The primary outcome measure is AVF primary patency at three months. Primary patency is defined as the unequivocal clinical presence of a thrill or audible bruit indicating flow through the fistula, in a fistula which has not required intervention to maintain or re-establish flow for whatever reason. Secondary outcomes include immediate post-operative patency (within one hour of termination of the procedure), primary patency at one month and one year, primary functional patency at three months and one year (that is, primary patency as described previously but which is also able to deliver flow greater than 350 ml/minutes without recirculation for the duration of haemodialysis), secondary patency at one year (that is, patency maintained by other therapeutic interventions, for example, interventional radiology), flow rates through AVF at one month, three months and one year, flow rates of the radial/brachial artery at one month, three months and one year measured by ultrasound, flow obtained at first HD, flow on HD after one year, change in cephalic vein diameter pre-/post-anaesthetic, change in radial or brachial artery flow pre-/post-anaesthetic, alteration of the surgical plan after anaesthetic and then venous/arterial mapping with ultrasound, AVF infection requiring antibiotics, pain during the procedure, pain one hour post-operatively, patient satisfaction, BPB success, complications including the requirement for conversion to general anaesthesia, the requirement for additional sedation or analgesics peri-operatively, post-operative paraesthesia or weakness suggestive of nerve damage, pneumothorax and time to perform the procedure.

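### Follow-up flow is named as brachial artery flow, but the single probe position set for all patients does not reach that artery in wrist and most forearm fistulae

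*Protocol article*

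**What the plan says.** Postoperative management of the protocol article names the artery for the three follow-up visits: "brachial artery volume flow will be measured (as a surrogate for AVF flow) by a blinded observer using Doppler ultrasound as described previously". It gives the reason: "Measurement of brachial artery flow is more reproducible than AVF flows and less prone to intraobserver variability". It then fixes the probe without distinguishing fistula types: "The probe will be positioned at a distance of 2 to 5 cm cranial to the arterio-venous anastamosis". For later visits it adds: "The point of measurement will be recorded and measurements at three months and one year made at the same position".

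Eligibility (Patients and enrolment) covers fistulae on either the radial or the brachial artery. Intra-operative management states: "All AVF procedures will be carried out at either the wrist, forearm or antecubital fossa". It describes both radio-cephalic and brachiocephalic procedures.

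Objectives and outcome measures lists flow through the fistula at the three visits and, as a separate entry, "flow rates of the radial/brachial artery at one month, three months and one year measured by ultrasound". Pre-operative management measures whichever of the two arteries will feed the fistula.

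On the choice of site, the text under Randomisation says, after describing the ultrasound mapping done once the anaesthetic is in: "The operating surgeon will use this information to decide on the final site for the fistula".

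**The concern.** The named artery and the probe position agree for a fistula in the antecubital fossa. They disagree for a fistula at the wrist, where a point a few centimetres above the anastomosis is still in the forearm. The observer must choose one instruction, and the article does not say which prevails.

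More than tidiness is at stake. If the distance rule is followed, brachial fistulae give brachial readings, and wrist and most forearm fistulae give radial readings, all under one outcome name. The final site is decided after the randomised anaesthetic, and the Background cites evidence that a block improves identification of the best site. The mix of arteries measured could therefore differ between arms for a reason that is not fistula flow.

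Flow matters to the interpretation of the trial. It is the proposed mechanism, the Abstract lists it among the secondary outcomes, and the sample size section suggests that the study is more than adequately powered for it. A difference in flow is therefore likely to be reported and read closely.

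**Working it through.** The protocol gives no figure for this point, so the check sets its statements side by side.

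**Step 1: the two instructions by fistula site.**

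| Fistula site | Artery named for follow-up | Artery under a probe 2 to 5 cm cranial to the anastomosis | Compatible? |
|---|---|---|---|
| Antecubital fossa (brachial) | Brachial | Brachial | Yes |
| Proximal forearm | Brachial | Usually radial; a very proximal anastomosis could bring the probe to the distal brachial artery | Mostly no |
| Wrist | Brachial | Radial | No |

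**Step 2: does another section resolve it?**
- Postoperative management refers back to the technique described earlier. Pre-operative management lets the artery depend on the fistula, which favours the inflow artery.
- The outcome list names both arteries with a slash, which also fits the inflow artery.
- The reproducibility argument in Postoperative management is specific to the brachial artery, which favours that artery for everyone.
- No section gives a separate rule for radial fistulae.

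Both readings can be defended and neither is stated to prevail.

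**Step 3: can the conflict affect the comparison between arms?** Suppose the distance rule is followed. Let s be the between-arm difference in the share of patients with a radial reading. Suppose the anaesthetic has no effect on flow other than through site. Then:

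difference in mean measured flow = s × (radial reading in radial fistulae − brachial reading in brachial fistulae)

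Adding and subtracting the brachial reading in radial fistulae splits this into two parts:
- s × (radial − brachial reading, both in limbs with a radial fistula). This is the measurement artefact; call the bracket D.
- s × (brachial reading in radial fistulae − brachial reading in brachial fistulae). This is a real consequence of a different site and would remain if the brachial artery were measured in everyone.

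Only s × D is artefact. If s = 0 there is no bias from this source, but the outcome still mixes two quantities.

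**Step 4: size.** The documents give neither s nor D. Under assumed values:
- s = 5% and D = 50 ml/min: 0.05 × 50 = 2.5 ml/min
- s = 20% and D = 200 ml/min: 0.20 × 200 = 40 ml/min
- s = 10% and D = 300 to 600 ml/min: 0.10 × 300 = 30 to 0.10 × 600 = 60 ml/min

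The spread from 2.5 to 60 ml/min comes entirely from the assumptions, and none of these values is an estimate.

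**Step 5: which outcomes are touched?** Primary patency rests on a thrill or bruit without intervention and uses no flow reading. Only the secondary ultrasound flow outcomes at follow-up are affected.

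**The case against.** The best reply is that the named target governs. An observer told to measure brachial flow would move the probe to the brachial artery, and no radial reading would arise. Alternatively, the inflow artery was meant throughout and the word brachial is loose. Either is possible, but the two replies point to different arteries, which shows that the text needs reconciling.

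Second, the safeguards. The observer is blinded, so which instruction is followed should not depend on arm once site is given. Three readings are averaged, and the point is recorded and reused. These help consistency within a patient. They do not make radial and brachial readings comparable between patients.

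Third, fistula site and measurement point are both recorded, and an analysis plan that is not shown could separate the readings. This stands in part: pooling is not certain. But brachial flow cannot be recovered once radial flow was recorded, and adjusting for site conditions on something decided after randomisation.

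Fourth, a change of plan may stay on the same artery. This stands, and it is one reason why s is unknown.

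A reader might also infer three stronger points that the documents do not support:
- That every radial fistula is affected. A very proximal forearm anastomosis may bring the probe to the brachial artery.
- That the whole difference between radial and brachial fistulae is artificial. Part of it may be a real site effect, and a change of surgical plan is itself a listed outcome.
- That radial patients lack a needed brachial baseline. The follow-up outcomes are flow rates, not changes from baseline, and the arterial change outcome compares before and after the anaesthetic.

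**Conclusion.** The contradiction stands as written: it is certain for wrist fistulae and holds for most forearm fistulae. It lies within one section of the article, and no other section resolves it. Because both instructions are stated and they conflict, this is not a detail left to an analysis plan.

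The effect on the comparison between arms is conditional. It requires that the distance rule be followed and that the share of radial readings differ between arms. Under those conditions part of the flow difference would be a measurement artefact, of a size and direction that the documents do not allow to be estimated. It would be wrong to conclude that the flow comparison is biased by a known amount, or that the trial's main result is in doubt: primary patency is unaffected. The point should be corrected because the remedy is cheap and the readings cannot be repaired afterwards.

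**What to change.** In Postoperative management, define the follow-up flow measurement at a stated landmark on the brachial artery in the upper arm for all fistulae. This keeps the protocol's own reproducibility argument. Limit the distance rule to antecubital fistulae, or remove it.

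If inflow-artery flow was intended instead, name the artery for each fistula type and do not pool radial and brachial readings as one outcome.

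In either case, align the two flow entries in Objectives and outcome measures with the choice, and say whether the one arterial reading serves for both. The existing rule on returning to the same position can stay, and no extra pre-operative brachial reading is needed.

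The cost is a change of wording to an ultrasound measurement that is already planned, with no added visit or scan. It has to be made before follow-up readings are taken.
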